## Abstract

**Background:**

As of September 2014, Kenya implemented the WHO recommended Option B+ guidelines in which all newly diagnosed HIV-infected pregnant women are immediately eligible for triple antiretroviral therapy (ART) for life regardless of CD4 count. In addition, Kenya previously established the Kenya Mentor Mother Program (KMMP) in 2012 to improve peer education and psychosocial support services within the national prevention of mother-to-child transmission (PMTCT) program. The primary objectives of the study described in the current protocol are: (1) to evaluate implementation of these new guidelines (Option B+ with Mentor Mothers) as part of routine service delivery; and (2) to evaluate potential benefits of a package of services within the KMMP (called EMMA) to improve PMTCT service delivery.

**Methods:**

We will conduct a cluster randomized controlled trial in western Kenya. We will allocate 12 clinics providing PMTCT services including ART to two study arms using pair matching: the standard of care (SOC) arm, which includes the KMMP as implemented by the clinics; and the intervention arm, which is the SOC (including KMMP) with the EMMA package of services (a targeted exit interview, visit reminders, and targeted follow-up). At the intervention clinics, the EMMA package of services is implemented as part of routine service delivery. A total of 360 (180 in each arm) pregnant women will be enrolled in the study at or near their first visit for antenatal care for prospective records review through 72 weeks post-partum. The primary and secondary outcomes are uninterrupted supplies of ART medications throughout the PMTCT cascade of care as well as infants completing HIV testing on schedule.

**Discussion:**

The EMMA package of services provides specific structure to the use of Mentor Mothers within PMTCT programs. This strategy was developed in collaboration with local health facility and PMTCT program staff based on their experience providing PMTCT services within the integrated ART-MCH facilities. If successful, this approach has the potential to improve dramatically PMTCT service delivery with minor additional costs beyond the basic mother–mentor program and support global goals to eliminate mother-to-child transmission.

**Trial registration:**

ClinicalTrials.gov, NCT02848235. Registered on 19 July 2016.

**Electronic supplementary material:**

The online version of this article (10.1186/s13063-018-2975-y) contains supplementary material, which is available to authorized users.

## Background

### Background and rationale

In Kenya, HIV-infected pregnant women should receive prevention of mother-to-child transmission (PMTCT) services, beginning with their first visit for antenatal care and lasting through 18 months after delivery (or cessation of breastfeeding with could occur later than 18 months). As of 2014, the Kenyan Ministry of Health recommended “Option B+” to be included into the standard PMTCT package of care, which includes the “immediate initiation of life-long ART in pregnant and breastfeeding women upon HIV diagnosis with continuous adherence support” (p. 16, [1]). The 2014 recommendations also concluded that “deliberate and focused patient support and defaulter tracking mechanism need to be put in place to ensure compliance to HIV treatment” (p. 16, [1]). As of September 2016, the Kenyan Ministry of Health reaffirmed its commitment to Option B+ and expanded the frequency of HIV testing for HIV-exposed infants (infants born to HIV-positive mothers) to 6, 24, 48, and 72 weeks [2].

Before 2016 in Kenya, treatment guidelines have been very specific on when to initiate antiretroviral therapy (ART) and what to initiate (which medications). Guidelines have been less explicit on where women should initiate and be managed on life-long ART during pregnancy and breastfeeding. Recognizing the barriers pregnant women newly diagnosed with HIV during antenatal care would face if they were referred elsewhere for HIV care and treatment, in 2005 the Kenyan South Rift Valley PEPFAR (SRVP) program began to integrate all HIV-related care, including ART, into PMTCT services provided at the larger maternal and child health clinics within the region. This was an early and innovative approach that is consistent with newer ideas for differentiated service delivery (DSD) or differentiated models of care (DMC) [3]. As of 2013, when the study described in the current protocol was being developed, this approach was implemented in the largest facilities providing PMTCT services in the SRVP.

As part of the standard of care (SOC) beginning in 2012, Kenya also developed the Kenya Mentor Mother Program (KMMP) [4], which follows on similar approaches implemented in other countries (e.g. see [5–7]). Mentor Mothers are clinic staff members who are also women living with HIV. They are trained and employed to be part of the clinic’s medical team to provide pre-test group education sessions, one-on-one and couples counseling, support groups, and defaulter tracking. As part of their routine clinic activities, Mentor Mothers obtain consent from their clients for various forms of follow-up, including consent for both phone and SMS follow-up (or only phone follow-up or no follow-up) as well as consent for home follow-up by her or a community health worker.

Information continues to be lacking in Kenya and elsewhere on the ability of PMTCT programs to initiate pregnant women with HIV on ART during pregnancy and retain them on treatment along the PMTCT cascade of care through delivery, cessation of breastfeeding, and for the longer term. What information exists suggests significant room for improvement. For example, a recently published study from a treatment program in western Kenya, with an active outreach department, reported that 32% of women initiated on ART during pregnancy disengaged from treatment before delivery [8]. Although the data for this study were from 2006 to 2009, they indicate the difficulties with retaining pregnant women on ART during pregnancy. Information on other key outcomes, such as the proportion of those eligible who actually initiated treatment are not reported. Another study from roughly the same region of Kenya during the same time period reported that 38% of women newly diagnosed with HIV during pregnancy did not register in the PMTCT program [9]. In two hospitals between Kericho and Nairobi (Gigil and Naivasha), only 4% of women eligible for ART initiated treatment within six months of their HIV diagnosis [10].

Some evidence suggests that integration of ART within maternal and child health (MCH) clinics, such as exists within the study region, improves linkage to and initiation of treatment. For example, a study from Zambia found that integration of PMTCT services including ART into MCH services increased the percentage of women who initiated PMTCT care (44% compared to 25%) and increased the percentage of those eligible who initiated treatment during pregnancy (32% compared to 4%) [11]. While integration improved upon these basic outcomes, the majority of patients still did not initiate PMTCT care or initiate ART if eligible. Early evidence on the implementation of life-long ART for pregnant women from Malawi suggests that eliminating CD4 counts as an eligibility criterion might facilitate initiation, but some significant share may still not agree to initiate ART and retention on treatment during and after delivery may remain problematic without specific attention directed towards these issues [12].

To support effective implementation of the Kenya PMTCT SOC in the South Rift Valley and other regions of Kenya, better and up-to-date information on implementation is still needed. Recognizing the importance of both timely initiation and retention on treatment during and after pregnancy, active strategies for retaining patients in care are preferable to after-the-fact follow-up to re-engage a patient in care who previously disengaged. Thus, feasible programmatic interventions can support successfully implementation of the SOC and long-term patient care beyond pregnancy.

The study described in the current protocol is designed to fill this information gap and to improve implementation of the Kenyan PMTCT SOC (which includes Option B+ and Mentor Mothers). We will evaluate the impacts of an innovative strategy to improve implementation of the SOC. The strategy, called the *E*nhanced *M*entor *M*other Progr*A*m (EMMA), provides specific structure to the use of Mentor Mothers within PMTCT programs. If successful, this approach has the potential to improve PMTCT service delivery and support global goals to eliminate mother-to-child transmission. This enhancement to the existing Mentor Mother program is consistent with the KMMP guidelines, which emphasizes that “the National Guidelines do not intend to remove the space for creativity and innovation in these approaches. On the contrary, the MOH hopes to inspire ongoing dialogue about quality improvements from the clearly defined starting point outlined herein” [4].

### Trial design

We will conduct a parallel, two-arm, cluster randomized controlled trial to examine the effect of the EMMA strategy on retention in the PMTCT cascade of care among HIV-positive pregnant and postpartum women, as well as HIV-exposed infants completing HIV testing on schedule. In addition, the cost to clinics of organizing and managing the revised Mentor Mother daily activities to provide EMMA services will also be assessed. A cluster randomized design is required as enhanced service delivery is implemented at a site level rather than at an individual patient level (see, e.g. [13] for additional discussion of study designs for quality improvement evaluations). The study will enroll patients in both study arms for prospective review of medical records and other information collected by the sites as part of routine patient care.

This study protocol follows the Standard Protocol Items: Recommendations for Interventional Trials (SPIRIT) guidelines (see Additional file 1 – SPIRIT Checklist).

### Description of the EMMA intervention

Before providing additional information on the study design and methods, it is useful to provide additional detail on the EMMA intervention first. Sites randomized to the SOC arm will continue to implement the Kenyan PMTCT SOC for all patients. Sites randomized to the intervention arm will implement EMMA as an addition to their SOC during the study period for all patients. Each pregnant woman with HIV presenting for antenatal care will receive the site’s SOC (including the KMMP) with the following additions:Exit discussion with the Mentor Mother

At the end of each MCH clinic visit, from the first ANC visit through 18 months post-partum, all women with HIV will be directed to a Mentor Mother**.** For perspective, sites typically have 1–2 Mentor Mothers. In the KMMP, the SOC does not specify the frequency at which one-on-one counseling should occur, only that at least one should occur over the course of a patient’s pregnancy. With EMMA, the Mentor Mother will complete an exit discussion/counseling session with the patient, at the end of each visit, to review clinical care received at the visit, answer questions, discuss any concerns of the patient, review the schedule for her next visit, and discuss the importance of attending the next visit (see Additional file 2 – Mentor Mother Guide).2.Reminder messages

At each exit discussion, the Mentor Mother will give each woman the option to receive an automatic text message from the Mentor Mother’s smartphone (Android) before her next visit (on a day and time of her choosing) to assist with planning for the visit. The message will say, “This is your reminder for your MCH visit on ‘DAY’, ‘DATE’”. This message option will be offered to women at each encounter because visit schedules are not standard for all patients and vary by gestational age, time after delivery, mothers’ and/or babies’ health, etc. The patient can opt to receive a text message at some visits but not others. If the patient does not have a cell phone, she can have a message sent to any other phone she would prefer. The Mentor Mother will also offer to set up a reminder directly in the patient’s cell phone on the date and time she would like the reminder to show on her phone (acts like a text message in an alarm). The Mentor Mother will also set up an automatic reminder on her cell phone for the day a patient is expected to return. In Kenya, the recipient of a text message incurs no cost. Text messages will be sent using SMS Scheduler, which is a free Android-based application that is installed on a study-purchased Smart phone provided to the Mentor Mother. This app was preferred by the study team due to its ability to store message delivery status and dates, which can be accessed periodically by the study team to document the reminders sent to each patient.3.Patient follow-up

If the patient does not return to the clinic at a scheduled visit, the Mentor Mother will wait for an additional day to see if the patient returns. If she does not, she will send a text to the patient and call the patient to follow-up (and counsel to return).

The EMMA intervention was developed in collaboration with local health facility and PMTCT program staff based on their experience providing PMTCT services within the integrated ART-MCH facilities. The intervention was designed to be: (1) feasible for sites to implement as an addition to routine practices; (2) already consistent with policies for patient management, interactions, and follow-up in Kenya; and (3) affordable for sites to adopt as routine practice. In short, this is an implementation science study that addresses how to improve implementation of an already know effective intervention, ART [14].

A number of other approaches were explored to optimize implementation of the 2016 SOC, such as subsidizing transportation costs, various incentives for completing visits on schedule (e.g. for six-week infant HIV testing), or automatic text messages for multiple future visits that could be set up without the Mentor Mother interaction with the patient. After reviewing such options in detail with program and site staff, such approaches were not considered feasible for sites to implement in the future as part of routine practice.

### Objective

The objective of this study is to assess adherence to scheduled clinic visits, retention in care, and infant HIV testing along key segments of the PMTCT cascade and the effect of EMMA on retention from study enrollment at or near the first visit for antenatal care through 18 months post-partum. In addition, the study will estimate the additional cost to the PMTCT program of implementing the EMMA strategy.

## Methods

### Study setting

We selected 12 health facilities providing integrated MCH and ART services in the study region as part of the Kenya Medical Research Institute (KEMRI)/Walter Reed Project (WRP) SRVP. These facilities provide the majority of PMTCT services for HIV-infected pregnant and post-partum women in the region. This region is ideal for this study for several reasons, including: all study sites are implementing the 2016 SOC; each site is a major MCH clinic providing PMTCT services in the region; ART services are already integrated into MCH services in all sites; the sites are geographically distributed across the region in Kisumu, Siaya, Kericho, Nandi, Bomet, and Narok Counties; and strong support in the region exists for study (from County Governments, KEMRI/WRP Community Advisory Board, and sites).

### Study population

The study population comprises all pregnant women with HIV presenting at a study site for their first antenatal care (ANC) visit. This includes women who are newly diagnosed with HIV as part of their first ANC visit (which is routine practice in the region and study sites) as well as pregnant women with HIV who are already on ART at their first visit for antenatal care.

#### Inclusion criteria

Adult patients (aged 18 years or older);Pregnant women with HIV presenting for antenatal care at a study site;The ability to understand and the willingness to sign/mark a written informed consent document in English, Kiswahili, or Luo during first or second visit for antenatal care at a study site.

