**Map 1 Fig1:**
[figure not shown]
Location of study sites (numbers 1 - 12)

Clinics in the intervention arm provide EMMA services to all patients at the study site, so providers are not blind to their treatment assignment. The study, however, enrolls a subset as study participants for prospective records review. Thus, patients are not blinded but all patients at the intervention sites are provided with EMMA services. After enrollment in the study, individuals receive the same services as provided to all patients at their clinic.

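### Allowing consent at the second antenatal visit selects part of the sample on a return that EMMA has already promoted; the effect is partial and cannot be sized from the article

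*Protocol article*

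**What the plan says.** Study population in the protocol article sets the starting point: "The study population comprises all pregnant women with HIV presenting at a study site for their first antenatal care (ANC) visit". The Inclusion criteria then allow written consent "during first or second visit for antenatal care at a study site". The Abstract and the Objective section likewise place enrolment at the first visit or close to it, so the window is deliberate.

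EMMA does not wait for consent. Description of the EMMA intervention says that "from the first ANC visit through 18 months post-partum, all women with HIV will be directed to a Mentor Mother", and Allocation to study arms confirms that "Clinics in the intervention arm provide EMMA services to all patients at the study site". Much of the content concerns the next appointment. The exit session is to "discuss the importance of attending the next visit", a reminder is offered, and a missed visit triggers a text and a call.

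Recruitment and enrollment describes the usual route: women hear of the study at their first visit, see study staff, consent, and only then go to the Mentor Mother. Data analysis compares enrolled women according to the arm of their site.

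**The concern.** A woman who consents at visit 2 has, by definition, come back. At an EMMA site she has already had the exit counselling and the offer of a reminder, and a text and call if she was late. Her entry to the study therefore depends on an event after allocation that the intervention is built to change. A woman who did not consent at visit 1 and never returned is not counted in either arm, and if EMMA works there will be fewer such women in the EMMA arm.

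Analysis by allocated arm does not repair this, because the selection happens before a woman joins the analysis set. The order in Recruitment and enrollment (consent first, Mentor Mother second) protects only visit-1 consenters.

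The outcomes most exposed are those whose clock starts at or close to visit 1: P1 (ART coverage between starting treatment and delivery) and S1 (starting ART within 30 days of the first visit). Part of any early retention benefit could be lost from the estimate.

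**Working it through.** **The plan's own figure.** The article states no number for this point. Table 1 supplies a base case, and it reproduces. For 0.40 vs 0.65 (5% two-sided, 80% power, continuity correction) the unclustered size is 70 per arm. With ICC 0.05 and 6 clusters per arm, m = 70 × 0.95 / (6 − 70 × 0.05) = 66.5 / 2.5 = 26.6, rounded up to 27. The design effect is 1 + 26 × 0.05 = 2.30, and 70 × 2.30 = 161. The illustration below uses 0.40 vs 0.65 as the true first-visit contrast.

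**Inputs.**
- From the article: P1 proportions 0.40 and 0.65; 180 women per arm.
- Assumed: r, the probability of returning for visit 2 in each arm; f, the share of the first-visit cohort whose enrolment would be deferred to visit 2, equal in both arms and unrelated to return; women who do not return fail P1.

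**Formula.** A fraction 1 − f is enrolled at visit 1 whatever happens later. A fraction f is enrolled only if the woman returns. Non-returners contribute no successes, so

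observed proportion = first-visit proportion / [(1 − f) + f × r].

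Example (return 80%/90%, f = 0.50): SOC 0.40 / (0.50 + 0.40) = 0.444; EMMA 0.65 / (0.50 + 0.45) = 0.684; difference 0.240.

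| Return SOC / EMMA | f | SOC observed | EMMA observed | Difference (true 0.25) |
|---|---|---|---|---|
| 90% / 95% | 0.25 | 0.410 | 0.658 | 0.248 |
| 80% / 90% | 0.25 | 0.421 | 0.667 | 0.246 |
| 80% / 90% | 0.50 | 0.444 | 0.684 | 0.240 |
| 80% / 90% | 1.00 | 0.500 | 0.722 | 0.222 |
| 70% / 90% | 0.25 | 0.432 | 0.667 | 0.234 |
| 70% / 90% | 0.50 | 0.471 | 0.684 | 0.214 |
| 70% / 90% | 1.00 | 0.571 | 0.722 | 0.151 |

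**Limiting case: EMMA acts only on first return.** Take return 70% and 90%, with P1 success 0.60 among returners in both arms. The true proportions are 0.70 × 0.60 = 0.42 and 0.90 × 0.60 = 0.54, a difference of 0.12. The observed difference is 0.100 at f = 0.25, 0.074 at f = 0.50 and 0 at f = 1. If the women brought back only by EMMA do less well (success 0.40), the true difference is 0.42 + 0.20 × 0.40 − 0.42 = 0.08. At f = 1 it becomes 0.50 / 0.90 − 0.60 = −0.044.

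**Direction.** In this model the risk ratio always moves toward 1 when EMMA raises return, because the SOC denominator shrinks more. The risk difference moves toward zero in every row above, but this needs a material gap in return. With 80% in both arms and f = 1, the observed values would be 0.40 / 0.80 = 0.500 and 0.65 / 0.80 = 0.8125, a difference of 0.3125. That is why the direction is probable, not certain.

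**The case against.** The strongest reply is that visit 2 is a fallback. Recruitment and enrollment has every woman informed at her first visit, and nothing in the article suggests that a large share consents later. Standard care already includes Mentor Mothers and defaulter tracing, so the gap in first return may be modest. EMMA also acts at every visit through 18 months, so first return is only one route to a P1 effect. With return of 80% and 90% and a quarter to a half of the cohort deferred, a 25-point effect loses only 0.4 to 1.0 points. All of this stands as an argument about size. It does not remove the selection.

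Three stronger readings are tempting and are not supported:

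- **That early dropouts are removed from both arms altogether.** Those who consented at visit 1 remain in the analysis; only women not yet consented can be lost in this way.
- **That the effect is halved, or some other fixed fraction.** This needs invented return rates, an invented visit-2 share and an assumption that EMMA works only through first return. The 32% disengagement cited in the Background cannot stand in for non-return to visit 2: it is cumulative loss before delivery among women started on ART in 2006–2009.
- **That Study population and Inclusion criteria contradict each other.** The first names the source population and the second the consent window. A visit-2 consenter may well have presented for a first visit at the same site.

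It is also fair to say that a sensitivity analysis is commonly left to the statistical analysis plan, which is not shown. Its absence here is not the finding. The finding is the stated enrolment rule.

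**Conclusion.** The point holds in limited form. Visit-2 consent conditions part of the enrolled sample on an event that EMMA is designed to change, and analysis by site arm cannot undo it. The loss is partial, P1 and S1 are most exposed, and the bias probably runs toward no effect, provided EMMA materially raises first return.

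The size cannot be fixed from the article. Under the assumed inputs, a true 25-point difference stays almost whole (24.8 points at 90%/95% return with a quarter deferred) or falls to 15.1 points (70%/90%, all at visit 2). Where first return is EMMA's only route and returners do equally well in both arms, the effect among visit-2 enrollees is zero. All of these rest on assumed return rates and visit-2 shares, and on non-returners failing P1. The planned sample of 360 is not affected.

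**What to change.** 1. Derive the visit of consent for each participant from the consent date and the visit dates already extracted on the mother's form.
2. Report the numbers enrolled at visit 1 and visit 2 by arm.
3. Prespecify an analysis of P1–P3 and S1 limited to women who consented at the first antenatal visit before any Mentor Mother contact, and read it alongside the main analysis.

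The cost is one further analysis with fewer women and wider intervals. With return of 80%/90% and f = 0.50, visit-1 consenters would be 0.50 / 0.90 = 55.6% of the SOC arm (100 of 180) and 0.50 / 0.95 = 52.6% of the EMMA arm (about 95 of 180). This analysis does not correct for any difference between arms in who agrees to consent at visit 1.

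Seeking consent at visit 1 wherever possible is reasonable. Banning visit-2 consent partway through recruitment is a trade-off and is not required. It could shut out women who learn their HIV status at that first visit and are not ready to consent the same day. Sites also started at different times: the enrolment order in Allocation to study arms averages (1 + 3 + 4 + 5 + 9 + 10) / 6 = 5.3 for EMMA and (2 + 6 + 7 + 8 + 11 + 12) / 6 = 7.7 for SOC. A new rule could therefore cover different shares of recruitment in the two arms.
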